#### c. STATISTICAL METHODS TO BE UNDERTAKEN

The analysis can be considered in 3 parts, aligned with primary and secondary hypotheses:

- i. **Primary outcome and hypothesis: Comparing brain volumes between stroke participant groups:** Primary outcome will be analysed on an intention to treat basis, The difference in brain volume from baseline to 4 months will be analysed using an ANCOVA model with exercise intervention group as a factor (e.g., Physical fitness training vs. Balance training groups), with baseline brain volume and functional status as co-variants (dichotomised as mRS = 0-1, 2 and 3).
- ii. **Secondary outcome and hypotheses: Correlating brain volume with blood pressure control and incident stroke:** Secondary outcomes will be analysed using appropriate repeated measures random effect logistic regression models with dichotomised hypertension status or silent/recurrent brain infarction (as defined in methods) as dependent variables, treatment group as independent variable, and functional status dichotomized as a covariate (as above). The initial regressive analysis will examine the

differences between participants with good and poor blood pressure control, using this as a binary measure. The presence of incident subclinical stroke will also be included as a binary variable. In the regional volumetric analyses, total brain volume, regional white matter, cortical and subcortical grey matter volume changes will be modelled using this design.

- iii. **Exploratory analyses: Independent effects of exercise on blood pressure, incident stroke, diastolic cardiac indices, and aerobic capacity:** Exercise effects on end-organ function and fitness (i.e., aerobic capacity) are likely dissociable, however emphasise that this component is exploratory. For the purposes of these analyses, we define each of our end-organ metrics as: brain volume, cognitive function, incident stroke, diastolic cardiac indices, aerobic capacity (VO2max), sleep duration, onset latency, bedtime/rise time variability (minutes), and sleep efficiency (%). Exploratory analysis will be conducted using appropriate regression models to investigate the associations between BP, incident stroke, diastolic cardiac indices, aerobic capacity. In addition, mediation analyses will be conducted to explore the possible mediating role of sleep in preservation of brain volume.

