## **b. INTRODUCTION**

The evidence is compelling: vascular burden is the greatest determinant of late life cognition. The imaging hallmark of neurodegeneration is brain atrophy. Cerebrovascular disease is associated with accelerated rates of structural brain aging, such as atrophy and white matter ischaemic burden. We have demonstrated increased rates of total and regional brain atrophy following ischaemic stroke [1-3]. Patients lose brain volume at a greater rate than control participants, and this volume loss is correlated with cognitive deficits. But not everyone atrophies at the same rate, and not everyone dement. The major risk factors that have emerged for post-stroke brain atrophy and cognitive decline are recurrent stroke, hypertension, and low rates of physical activity.

In this project, we will examine these modifiable risk factors that may predict post-stroke brain atrophy. Using brain volume and brain connectivity measures at 4 months and 12 months after stroke, we will examine the effects of a targeted cardiovascular home-based exercise intervention on brain volume. We will chart cumulative vascular burden via advanced brain imaging, ambulatory blood pressure (BP) monitoring, and interrogate the links between activity levels, hypertension, cardiac diastolic dysfunction, cognition, aerobic capacity (i.e., fitness), diet, gut microbiome, and key physiological biomarkers.

The original PISES Study demonstrated good retention and attendance rates, but we found two major factors have hindered recruitment. Over one third of people approached to participate listed 'inconvenient program location' or 'time commitment demanding' as reasons for not participating. The impact of COVID-19 has further limited uptake in a centre-based intervention. In response, PISCES-ZODIAC has been designed to overcome these barriers by delivering the intervention via one-on-one telehealth consult in the convenience of the participant's own home by a trained exercise professional.

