### **c. RANDOMISATION**

After the first time-point assessments, participants will be randomly allocated into one of two exercise groups using a computer generated schedule with permuted blocks of various sizes. This will be part of the electronic case report form (ECRF) hosted at a secure server at the Florey and compliant with Good Clinical Practice (GCP) guidelines for clinical trials. The randomisation will be stratified by baseline function (modified Rankin Scale score, grouped into mRS 0-1, 2-3) and baseline total brain volume (low, high).

Participants will be aware of their group allocation based on the exercise programme they are administered. Investigators who are blind to participant group will conduct cognitive testing, MRI analysis, and cardiovascular testing.

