#### **I.b. Demographic and medical history questionnaire**

The research team has developed the study questionnaire. It will be used to obtain only the most pertinent demographic, medical, and psychiatric information required for this study. The questionnaire will be cross-checked for accuracy by medical record review if the participants have attended Austin Health, Eastern Health, Western Health, or Epworth Camberwell. The questionnaire will include questions on general health, cardiac risk, history of cognitive decline, hypertension, presence of dyslipidaemia, cardiac disease (MI, angina, HF, previous angioplasty and/or bypass surgery), and other macro-vascular complications (previous stroke or transient ischaemic attack, peripheral vascular disease). Age, sex, diabetic status,

and smoking history, drug therapy (antihypertensives, renin angiotensin system (RAS) inhibitors, statins) as well as family history of cardiovascular disease will be recorded.

In addition to the demographic questionnaire described above, study investigators will obtain information about participants' musical background (e.g., what instruments they have ever received training on, and for how long) using The Survey of Musical Experience [46]. An increasing amount of evidence now suggests that music training might be protective for the brain. For example, musicians have been found to perform better on tests of verbal and working memory, and executive functions [47-49], and music training has been associated with both structural and functional changes in multiple regions of the brain [50,51]. This may represent a possible confound for the current study, in determining the differences and changes in brain volume between and within the two exercise training groups that might be attributable to the exercise programmes versus pre-existing potential neuroprotective factors. While the impact of music expertise on cognition has been investigated in single case studies of individuals with stroke, to our knowledge, there currently exist no group studies examining this link, nor studies investigating the association between prior music training and brain volume in stroke.

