## 6. STUDY POPULATION

### a. RECRUITMENT PROCEDURE

120 newly acquired ischaemic stroke participants (i.e., <2 months post-ischaemic stroke) will be recruited from the Austin Health, Eastern Health, Western Health, and Epworth Camberwell Stroke Units and followed longitudinally. All ischaemic stroke subtypes will be included. Several methods will be used to recruit participants over the 3 year recruitment period of the study:

- a) The Principal Investigator ([name]) holds clinical appointments at both Austin Health and Eastern Health Stroke Units.
- b) Senior clinicians on all Stroke Units will be notified of the study and asked to identify potentially suitable participants.
- c) Study investigators will attend ward rounds and clinical meetings to identify potentially suitable participants.

In each case of the above, potential participants will be approached with the guidance of [name] or the senior inpatient ward clinician. The study investigators will speak to potential participants and provide them with verbal and written information on the study.

Participants will be screened to ensure that they are cognitively able to participate in the study and have no contraindication to the MRI. The investigators will screen potential participants using a short, semi-structured questionnaire. If the recruiter is unsure whether the potential participant has the cognitive capacity to participate, the opinions of the study neuropsychologist will be obtained.

Demographic and medical information including age, gender, medication status, side and site of stroke and admission stroke severity (National Institutes of Health Stroke Scale, NIHSS) and functional status (modified Rankin Score, mRS) will be obtained.

1001                   b. INCLUSION CRITERIA

1002 120 participants who recently acquired ischaemic strokes (i.e., ischaemic stroke <2 months)  
1003 will be recruited. All ischaemic stroke subtypes will be included.

1004  
1005 Participants will be included if the following eligibility criteria are met during the initial  
1006 screening:

- 1007 • Ischaemic clinical stroke patient (first or recurrent stroke) aged greater than 18 years;
- 1008 • Cardiac function not precluding exercise intervention;
- 1009 • Premorbid mRS<3, denoting no, mild or moderate disability; and
- 1010 • Able to give consent; and
- 1011 • Able to nominate an emergency contact person.

1012                   c. EXCLUSION CRITERIA

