#### b. POWER CALCULATIONS

The total sample size of 120 participants will yield 80% power to detect a difference corresponding to a medium to large effect size on brain volume measures, assuming the standard settings of 2-tailed significance,  $\alpha=0.05$ , and  $d=0.6$ . This effect size is reasonable, given that in our CANVAS pilot data, we reported hippocampal and total brain volume loss of -3% and -1.5% respectively over one year, in contrast to the control change of -0.4% and -0.6% over the same time period.

We have increased the sample size by 30% to cover attrition over the 12 month period and the possibility of non-evaluable scans (e.g., movement, etc.) giving  $n=60$  per group.

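### Optional refinement: adding age, which is already recorded, to the covariates of the primary ANCOVA could buy a small gain in precision at almost no cost

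*Protocol*

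**What the plan says.** Section 8.c(i) of the protocol states the primary model: "The difference in brain volume from baseline to 4 months will be analysed using an ANCOVA model". Exercise group is the factor, and the model is fitted "with baseline brain volume and functional status as co-variants". Functional status enters as a two-level mRS variable. The analysis is by intention to treat.

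These covariates match the randomisation scheme in section 5.c, which is "stratified by baseline function (modified Rankin Scale score, grouped into mRS 0-1, 2-3) and baseline total brain volume (low, high".

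Age is available. The demographic and medical history questionnaire (5.d, I.b) lists "Age, sex, diabetic status" among the items recorded, and the recruitment procedure (6.a) collects "Demographic and medical information including age, gender, medication status, side and site of stroke and admission stroke severity". The study is open to adults over 18 with no upper age limit, so the age range may be wide.

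The power calculation (8.b) uses "2-tailed significance", alpha 0.05, d = 0.6 and 80% power, with 60 per group after a 30% increase. It mentions no gain from covariate adjustment.

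**The concern.** In a randomised comparison of a continuous outcome, adjusting for a baseline variable that predicts the outcome shrinks the residual variance and so the standard error of the treatment effect. It also takes account of any chance imbalance in that variable. Age is a natural candidate when the outcome is brain volume loss, it is already collected, and neither the strata nor the model uses it.

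Baseline volume may not fully stand in for age. The modelled outcome is change, and age could relate to the rate of loss separately from the starting level. The protocol describes no head-size correction for total brain volume, so the low/high volume stratum need not balance age closely.

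Only efficiency is at stake: a slightly narrower interval and slightly higher power for the same number of participants.

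**Working it through.** **Inputs from the protocol.** Two-sided alpha 0.05, power 80%, d = 0.6, a 30% increase for attrition and non-evaluable scans, 60 per arm (8.b). Covariates are baseline volume and two-level mRS (8.c(i)).

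**Inputs assumed.** The partial R² of age with volume change, given baseline volume and mRS, is not in the protocol. We take 2%, 5% and 10%, with 1% as a low case. We also read d = 0.6 as standardised on the residual SD of the model as it now stands, since 8.b gives no SD.

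**Step 1: reproduce the plan's sample size.** A two-sample t-test with d = 0.6, alpha 0.05 and 80% power needs 44.6, so 45 per arm. Increased by 30%: 45 × 1.3 = 58.5, close to the stated 60. The stated size reproduces and does not depend on age.

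**Step 2: evaluable numbers in the pessimistic case.** 60 × (1 − 0.30) = 42 per arm, 84 in all.

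**Step 3: power without age.** The non-centrality is d × √(n/2) = 0.6 × √21 = 2.750 on 82 degrees of freedom, which gives power 77.6%.

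**Step 4: power with age.** Removing a share R² of residual variance gives d_adj = 0.6 / √(1 − R²). The standard error falls by 1 − √(1 − R²), and the equivalent gain in participants is 1/(1 − R²) − 1.

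| Assumed partial R² | d_adj | Non-centrality | Power, 42 per arm | Fall in SE | Equivalent extra participants |
|---|---|---|---|---|---|
| 0 | 0.600 | 2.750 | 77.6% | 0 | 0 |
| 1% | 0.603 | 2.763 | 78.0% | 0.5% | 1.0% |
| 2% | 0.606 | 2.777 | 78.4% | 1.0% | 2.0% |
| 5% | 0.616 | 2.821 | 79.6% | 2.5% | 5.3% |
| 10% | 0.632 | 2.898 | 81.7% | 5.1% | 11.1% |

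**Step 5: the cost of the extra covariate.** With 84 participants, estimating one more coefficient costs about 1/(84 − 5) = 1/79 = 1.3% in variance. A partial R² of about 1% or less (a partial correlation of roughly 0.11 or below, since √(1/79) = 0.11) therefore yields nothing useful. Step 4 does not deduct this cost, so its gains are slightly generous.

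**Step 6: is 42 per arm the right base?** Section 8.b says the 30% covers losses over 12 months as well as unusable scans, while the primary endpoint is at 4 months. If the loss by 4 months were 25% (assumed), 60 × 0.75 = 45 per arm remain and power without age is 80.4%. At 20% loss (assumed), 48 per arm give 82.9%. With no loss, 60 per arm give 90.3%.

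**The case against.** The strongest case against raising this at all is that the plan contains no mistake. The baseline value of the outcome plus the stratification variables is a coherent, pre-specified covariate set. The key premise is also not documented: no part of the protocol says or quantifies that age predicts change over about two months once baseline volume and mRS are in the model. The introduction says "The major risk factors that have emerged for post-stroke brain atrophy and cognitive decline are recurrent stroke, hypertension, and low rates of physical activity", and age is not on that list. Other recorded variables, such as sex, admission NIHSS and APOE, could be proposed by the same reasoning, and the protocol itself flags APOE and musical training, not age, as possible confounds. Finally, extra covariates are often settled in a statistical analysis plan, which is not at hand.

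Most of this stands, and it is why the point is an option and not a correction. Two qualifications apply. The protocol does give age some indirect standing: its background describes structural brain aging as accelerated by cerebrovascular disease, and the earlier cohort it builds on used controls matched on age and sex. The listed risk factors are introduced as modifiable ones, so age's absence there does not show that it is unimportant. In addition, 8.c(i) states its covariates outright and does not defer them, so the protocol is a sensible place to add one.

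A reader might infer more than this: that leaving age out biases the comparison, inflates the type I error, or lets a chance age imbalance invalidate the result. None of these follows. Randomisation protects the comparison, and the ordinary standard error already allows for chance imbalance.

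**Conclusion.** The primary ANCOVA is valid and unbiased as written. Adding age is a reasonable optional improvement in precision with a probably small return: about 1 to 4 points of power at 42 per arm for an assumed partial R² of 2% to 10% (77.6% rising to 78.4% to 81.7%), and essentially nothing at about 1% or less. The partial R² is an assumption throughout.

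It would be tempting to say that the trial falls short of 80% power and that adjusting for age is needed to rescue it. The documents do not support that. The shortfall appears only when the full 12-month loss is applied to the 4-month endpoint, and 45 evaluable per arm already give 80.4% without age. Nor do the documents show that a known amount of precision is being lost, because they give no figure for age's effect.

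**What to change.** Optionally, in 8.c(i), name age as a continuous covariate beside baseline brain volume and the two-level mRS variable. Do this before unblinding, so that the choice cannot depend on the results. If an analysis plan repeats the primary model, change it there too.

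The cost is one phrase and one degree of freedom. No new data, visits or participants are needed, and the sample size can stay as it is. If the sponsor prefers the present model, the primary analysis remains sound.

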### **Secondary hypothesis**

- i. Brain volume will be correlated with BP and incident brain infarction at 4 months and 1 year post-stroke;
- ii. Incident end-organ disease (silent or recurrent brain infarction, ambulatory blood pressure (BP), and cardiac structural disease) at 4 months and 1 year post-stroke will be reduced by aerobic exercise;
- iii. Incident physical activity levels, normotension, normal cardiac indices, higher aerobic capacity, and better sleep profiles will be associated with preserved brain volume at 4 months and 1 year post-stroke.

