## **b. STUDY AIMS**

Using brain volume and brain connectivity measures at one year after stroke, the aims of this research project are:

1. Examine the effects of home-based aerobic exercise intervention delivered at 2 months post-stroke on brain volume 4 months after stroke, and the stability of such effects at 1 year after stroke;
2. Document vascular burden using 3 end-organ effects: incident brain infarction, cardiac diastolic dysfunction, and ambulatory BP;
3. Examine the link between incident physical activity, aerobic fitness, sleep, and brain volume;
4. Examine the effects of exercise on blood pressure and cardiac diastolic function 4 months and 1 year after stroke;
5. Measure the change in BDNF and HbA1c levels 4 months and 1 year post-stroke and if exercise affects these;
6. Examine the association between physical activity, dietary intake, gut microbiome and brain volume.

An additional aim, which has been framed as a sub-study nested within the greater protocol, will enable us to capture any specific factors that influence participation in, or adherence to, post-stroke home-based exercise regimens.

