## **V. Ambulatory Blood Pressure and ECG monitoring**

24-hour ambulatory BP monitoring and 15-minute ECG-based heart rate variability for autonomic nervous system function assessment will be conducted for each assessment visit. Each participant will have a CardXplore monitor fitted for 24 hours. The CardXplore is a combined 24-hour ambulatory blood pressure and Holter ECG recorder. Trained staff will fit the monitor and explain the procedure to the participant. Analyses will be undertaken with the guidance of Associate [name] [name] in Clinical Pharmacology.

Circadian BP pattern classification will be based on the per cent decline in night-time BP compared with daytime BP. The normal ranges of ambulatory BP are defined as follows: daytime BP <135/85 mm Hg, night-time BP <120/75 mm Hg, 24-hour BP <130/80 mm Hg. For secondary hypotheses, statistical analysis will be performed using BP as a binary variable; i.e., abnormal BP, yes/no.

CardXplore monitors will be fitted during the first part of each timepoint so that the participant can return the monitor during the second part of each timepoint, which will minimise inconvenience to participants.

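### As listed, the repeated-measures model for hypertension status gives one common odds ratio, not the effects at 4 months and 1 year that the plan names, and it omits 2-month BP status

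*Protocol*

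**What the plan says.** **The model.** Section 8.c(ii): "Secondary outcomes will be analysed using appropriate repeated measures random effect logistic regression models with dichotomised hypertension status" or silent/recurrent infarction "as dependent variables, treatment group as independent variable, and functional status dichotomized as a covariate (as above"). The terms named are therefore treatment group and dichotomised mRS. Section 8.c(i), for the primary outcome, does name the baseline value of the outcome as a covariate. Section 8.c(ii) carries forward only functional status.

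**The question.** Secondary hypothesis ii (section 4.a) says that incident end-organ disease, including ambulatory BP, "at 4 months and 1 year post-stroke will be reduced by aerobic exercise". Aim 4 (section 4.b) is to "Examine the effects of exercise on blood pressure and cardiac diastolic function 4 months and 1 year after stroke".

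**The data.** Section 5.d(V) says that 24-hour BP monitoring and ECG-based "heart rate variability for autonomic nervous system function assessment will be conducted for each assessment visit". The procedures table in section 5.b lists ambulatory BP at baseline (2 months), 4 months and 1 year. For the secondary hypotheses, "statistical analysis will be performed using BP as a binary variable; i.e., abnormal BP, yes/no".

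**The timing of allocation.** Section 5.c: "After the first time-point assessments, participants will be randomly allocated into one of two exercise groups". The 2-month BP record therefore precedes allocation.

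**The concern.** In a repeated-measures logistic model, a treatment main effect without a visit interaction is one common log odds ratio over all outcome rows. The two follow-up times differ in kind. The 8-week programme starts at 2 months, so the 4-month visit falls at about the end of training, and the 1-year visit is about 12 − 4 = 8 months later. Whether an effect persists is an open question. For brain volume the protocol says so itself, since aim 1 asks about the effect "and the stability of such effects at 1 year after stroke". A single odds ratio cannot show whether an effect on hypertension seen after training is still there at 1 year.

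Two matters concern the 2-month record. First, BP status before randomisation is likely to predict later BP status. Leaving it out of the model gives up precision and leaves a chance imbalance between arms uncorrected. Second, the section does not say which visits supply outcome rows. No treatment effect can exist at 2 months, so if that record were an outcome row under a common treatment effect, it would pull the estimate towards no effect.

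**Working it through.** **Plan's own figure.** The protocol gives no effect size, event rate or power for this secondary model. Its 60 per group is derived for the primary outcome and has no bearing here.

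**Inputs from the protocol.** Binary BP status; records at 2, 4 and 12 months; allocation after the 2-month assessments; about 1:1 allocation; listed terms of group and dichotomised mRS.

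**Assumptions, not from the protocol.** Control-arm probability of abnormal BP 0.5 at random intercept zero; random-intercept SD 1.5 on the logit scale; the odds ratios (ORs) shown below. mRS was left out of the simulation for simplicity.

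**Model.** logit P(abnormal BP) = a + b_i + d × group, fitted by maximum likelihood, against the same model with visit and group-by-visit terms. One simulated data set of 20,000 participants was used per scenario, so small deviations from the true values are simulation error.

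| Outcome rows | True OR at 4 and 12 months | Group-only OR | ORs with group-by-visit terms |
|---|---|---|---|
| 4, 12 | 0.50, 0.50 | 0.51 | 0.51, 0.50 |
| 4, 12 | 0.50, 0.80 | 0.63 | 0.49, 0.79 |
| 4, 12 | 0.40, 1.0 | 0.61 | 0.38, 0.91 |
| 2, 4, 12 | 0.50, 0.50 | 0.63 | 1.04, 0.47, 0.49 |
| 2, 4, 12 | 0.50, 0.80 | 0.73 | 1.03, 0.49, 0.78 |
| 2, 4, 12 | 0.40, 1.0 | 0.74 | 1.01, 0.40, 0.98 |

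**Hand check.** The common log odds ratio is roughly the mean of the row-specific ones, so the pooled OR is near their geometric mean:
- 4 and 12 months, true 0.40 and 1.0: (0.40 × 1.0)^(1/2) = 0.63, against 0.61 fitted.
- With the 2-month row (OR 1), true 0.50 and 0.50: (1 × 0.50 × 0.50)^(1/3) = 0.63, against 0.63 fitted.
- With the 2-month row, true 0.40 and 1.0: (1 × 0.40 × 1.0)^(1/3) = 0.74, against 0.74 fitted.

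**Share of the log odds ratio lost with 2-month outcome rows and a constant effect.** 1 − ln(0.63)/ln(0.50) = 1 − 0.462/0.693 = 0.33.

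**Sensitivity.** A second simulation used random-intercept SD 2, 2,000 participants and the mean of six data sets:
- Constant true OR 0.40: 0.38 with follow-up rows only, 0.55 with 2-month rows added. The loss in the latter is 1 − ln(0.55)/ln(0.40) = 1 − 0.598/0.916 = 0.35.
- True 0.40 and 1.0: 0.65 and 0.72 respectively.
- True 0.40 and 0.70: 0.52 and 0.64 respectively.

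**Reading.** With follow-up rows only, a constant effect is recovered. An effect that differs between visits is replaced by a value between the two. Only the use of 2-month rows as outcomes dilutes a constant effect.

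**The case against.** The strongest reply is that section 8.c(ii) describes a class of model and not an equation. It speaks of appropriate repeated-measures models. It does not exclude a visit term, does not say that one pooled odds ratio will be reported, and does not say that 2-month records are outcomes. Coding of time is often left to a statistical analysis plan, which may exist. Hypothesis ii does not demand a separate test at each visit, and a common odds ratio over the two follow-ups is a legitimate summary if the effect is similar at both.

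Much of this stands, and it rules out three stronger readings that a reader might infer:
- *That hypothesis ii and aim 4 cannot be answered.* The wording leaves room for the missing terms. Aim 4 also covers diastolic function, which is not a dependent variable in this model. Section 8.c(iii) takes up exercise effects on BP, incident stroke and diastolic indices in exploratory regressions whose terms are left open.
- *That the plan will report a diluted effect.* The protocol does not make 2-month BP an outcome row, and hypothesis ii names only the two later times.
- *That the simulated losses measure this trial.* They rest on assumed odds ratios and random-intercept SDs. The largest shifts need either 2-month outcome rows or an effect that has vanished by 12 months.

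What does not fall away is that the section is not silent. It names the exposure and the covariate, and that list does not match the times in the hypothesis. It also leaves out the pre-randomisation value that section 8.c(i) includes for the primary outcome.

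**Conclusion.** The point holds in a limited form. The terms listed for hypertension status give one common odds ratio, while hypothesis ii and the BP part of aim 4 name two times, and 2-month BP status is not adjusted for. With follow-up rows only and a constant effect there is no bias. With an effect that differs by visit, the single figure describes neither visit. With 2-month outcome rows, about one third of the log odds ratio would be lost even under a constant effect. That last figure is illustrative and conditional on a choice the protocol does not state. The primary ANCOVA, the sample size and the diastolic-function analysis are not affected. This is a secondary analysis that should be tightened before unblinding, so that the choice between a pooled, a 4-month and a 1-year result is not made afterwards.

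**What to change.** For BP, restate the model in section 8.c(ii) as follows:
- outcomes: abnormal BP status at 4 and 12 months;
- fixed effects: treatment group, visit, treatment-by-visit;
- covariates: 2-month BP status (or value) and mRS stratum, with the 2-month record not used as an outcome row;
- random effect: participant;
- report: the arm contrast as an odds ratio with confidence interval at 4 months and at 12 months. A pooled odds ratio over the two follow-ups may be given as well.

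The cost is a change of wording. All the data are already scheduled. Each visit-specific estimate will be less precise than the pooled one. With about 60 per arm before attrition, the intervals for a binary outcome may be wide, which is a reason to keep the pooled estimate beside them.

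### The section 8.c.ii treatment-group models adjust for mRS only, although randomisation is also stratified by baseline total brain volume (minor)

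*Protocol*

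**What the plan says.** Protocol section 5.c stratifies the permuted blocks by two factors: mRS, "grouped into mRS 0-1, 2-3) and baseline total brain volume (low, high").

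Section 8.c, part i, analyses the primary outcome by ANCOVA, "with baseline brain volume and functional status as co-variants". Both stratification variables are therefore in the primary model.

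Section 8.c, part ii, specifies repeated-measures random-effect logistic models with "dichotomised hypertension status or silent/recurrent brain infarction (as defined in methods) as dependent variables". Their right-hand side is given as "treatment group as independent variable, and functional status dichotomized as a covariate (as above"). Baseline brain volume is not named. The same part ends by saying that total brain volume, regional white matter, and "cortical and subcortical grey matter volume changes will be modelled using this design".

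The synopsis does not restore the missing term. For the secondary regressions it names treatment group only.

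**The concern.** Stratifying on a prognostic variable balances the arms on it and so reduces the true variability of the treatment estimate. A model that omits the variable leaves the between-stratum variance in its residual, so the reported standard error does not reflect the balance achieved. The test then rejects less often than its nominal level, and the precision that adjustment could have given is lost.

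This is not detail that a protocol would simply leave for later. Part ii states a covariate set, carries one stratification factor over from part i by cross-reference, and drops the other. An analysis plan that followed the text would inherit the gap. At stake is some efficiency in the secondary comparisons of arms.

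**Working it through.** **1. Covariates side by side.**
- Section 5.c, stratification: mRS group (0-1, 2-3) and baseline total brain volume (low, high).
- Section 8.c.i: baseline brain volume and dichotomised mRS.
- Section 8.c.ii: dichotomised mRS only.

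**2. The plan's own sample size.** Section 8.b states "The total sample size of 120 participants will yield 80% power", "assuming the standard settings of 2-tailed significance", alpha 0.05 and d = 0.6, with a 30% increase.
- n per arm = 2 × (1.960 + 0.842)² / 0.6² = 43.6, so 44 (45 by the t-test).
- 44 × 1.3 = 57.2, so 58; 45 × 1.3 = 58.5, so 59. The stated 60 is reproduced to within 2 and is not in dispute.
- Evaluable number used below: 120 × 0.70 = 84, or 42 per arm.

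**3. Linear volume-change model, by formula.** Take the outcome SD as 1, and let r be the correlation of volume change with baseline volume. The protocol does not give r, so it is an assumption.
- Standard error without volume: √(2/42) = 0.218.
- Standard error with continuous baseline volume: 0.218 × √(1 − r²).
- r = 0: 0.218, no change.
- r = 0.3: 0.218 × 0.954 = 0.208, and 0.218 / 0.208 = 1.05.
- r = 0.5: 0.218 × 0.866 = 0.189, and 0.218 / 0.189 = 1.15.

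**4. The same by simulation.** Stratified permuted blocks, 84 participants, median split on volume, 40% in mRS 2-3 (assumed), no treatment effect, 4,000 runs. Monte Carlo error on a 5% rate is √(0.05 × 0.95 / 4000), about 0.3 points.

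| r | Covariates | Mean reported SE | Actual SD of estimate | Type I error |
|---|---|---|---|---|
| 0 | mRS | 0.217 | 0.215 | 4.4% |
| 0 | mRS + continuous volume | 0.218 | 0.215 | 4.4% |
| 0.3 | mRS | 0.218 | 0.214 | 4.6% |
| 0.3 | mRS + low/high volume | 0.212 | 0.214 | 5.3% |
| 0.3 | mRS + continuous volume | 0.208 | 0.209 | 5.2% |
| 0.5 | mRS | 0.218 | 0.202 | 3.4% |
| 0.5 | mRS + low/high volume | 0.199 | 0.202 | 5.5% |
| 0.5 | mRS + continuous volume | 0.189 | 0.190 | 5.6% |

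At r = 0.5 the mRS-only model reports 0.218 when the estimate actually varies by 0.202 (0.218 / 0.202 = 1.08). That mismatch is the conservatism. The rest is real lost precision: 0.202 / 0.190 = 1.06. At r = 0.3 the type I error is hardly distinguishable from nominal. The simulation allocates the 84 directly. Losses after randomisation would disturb the balance and bring the type I error nearer 5%, while the gap in reported standard errors would remain.

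**5. Logistic models.** Part ii plans a subject-level random effect. In the large-sample limit, with 2 or 3 visits, an intercept SD of 1 or 2 and a true log odds ratio of −1.099, omitting a volume stratum with odds ratio 4 gives −1.098 to −1.099. The random intercept absorbs a covariate that is constant within a participant. An ordinary single-visit logistic model would give −0.987, but that is not the planned model.

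**The case against.** Four points are fair.

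First, the wording that extends part ii to volume changes is loose. It follows sentences about good versus poor blood pressure control and incident stroke, under a heading about correlating brain volume with both. It could mean that volume change is compared by those groups and not by arm. An argument about stratified randomisation would then not apply to it. A reader might infer that total brain volume change is certain to receive two treatment estimates with different adjustment; the text does not settle that. The figures for volume change are therefore conditional on the other reading.

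Second, nothing in the protocol shows that baseline volume is prognostic for these outcomes. A reader might take secondary hypotheses i and iii as saying so. Hypothesis i correlates volume with blood pressure and infarction at 4 months and 1 year, and in iii preserved volume is itself the outcome. The only support is indirect: the sponsor stratified on volume and adjusted for it in the primary model.

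Third, a reader might expect odds ratios pulled towards 1. That holds for a single-visit logistic model but not for the random-intercept model planned here (step 5). Power figures from single-visit models do not carry over either.

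Fourth, these are secondary analyses without a power target, and d = 0.6 was set for the primary outcome, so no power loss is claimed here. An analysis plan not shown might add the covariate.

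These points limit the size and reach of the concern. They do not remove the mismatch between sections 5.c, 8.c.i and 8.c.ii.

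**Conclusion.** The point stands as minor. The covariate set stated in 8.c.ii omits one of the two stratification factors. Where baseline volume is prognostic, the comparison of arms is conservative and less efficient.

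For volume-change models that compare arms with the mRS-only set, the reported standard error is about 5% (r = 0.3) to 15% (r = 0.5) larger than needed, with a type I error of about 4% (4.6% and 3.4% in the table). At r = 0 nothing is lost. This rests on 84 evaluable participants, the assumed r, and the reading of 8.c.ii described above. For the random-intercept logistic models no meaningful attenuation of the odds ratio was found, and any power loss is unquantified.

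A reader might go further and conclude that the secondary tests have inflated error or that the primary result is weakened. Neither follows: the error is on the conservative side, and 8.c.i already carries both factors. Nor does the point reach the exploratory analyses in 8.c.iii, for which no covariate set is stated.

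**What to change.** In section 8.c.ii, state that every treatment-group comparison adjusts for both stratification factors, mRS group (0-1, 2-3) and baseline total brain volume. State also that any volume-change model comparing arms includes the baseline value of the volume analysed, in line with 8.c.i. The same sentence can say whether the volume-change models compare arms at all.

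The cost is one degree of freedom per model, or two for a regional volume model. No new data are needed, because allocation already requires baseline total brain volume for everyone randomised. If silent or recurrent infarctions are few, a penalised fit keeps the extra term from destabilising the logistic model.
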